## Abstract

**Background:**

Breast cancer is a global public health issue. The side effects of the clinical treatment can decrease the quality of life of these women. Therefore, a healthy lifestyle is essential to minimize the physical and psychological side effects of treatment. Physical activity has several benefits for women with breast cancer, and Pilates solo and belly dancing can be an enjoyable type of physical activity for women with breast cancer undergoing clinical treatment. The purpose of this study is to provide a Pilates solo and a belly dance protocol (three times per week/16 weeks) for women undergoing breast cancer treatment and compare its effectiveness with that in the control group.

**Methods:**

The participants will be allocated to either the intervention arm (Pilates solo or belly dance classes three times per week for 16 weeks) or a control group (receipt of a booklet on physical activity for patients with breast cancer and maintenance of habitual physical activity routine). The Pilates solo and belly dance classes will be divided into three stages: warmup and stretching, the main stage, and relaxation. Measurements of the study outcomes will take place at baseline; postintervention; and 6, 12, and 24 months after the end of the intervention (maintenance period). The data collection for both groups will occur with a paper questionnaire and tests covering general and clinical information. The primary outcome will be quality of life (EORT QLQ-C30 and EORT QLQ-BR23), and secondary outcomes will be physical aspects such as cardiorespiratory fitness (6-min walk test and cycle ergometer), lymphedema (sum of arm circumference), physical activity (IPAQ short version), disabilities of the arm (DASH), range of motion (goniometer test), muscular strength (dynamometer test) and flexibility (sit and reach test), and psychological aspects such as depressive symptoms (Beck Depression Inventory), body image (Body Image After Breast Cancer Questionnaire), self-esteem (Rosenberg), fatigue (FACT-F), pain (VAS), sexual function (FSFI), and sleep quality (Pittsburgh Sleep Quality Index).

**Discussion:**

In view of the high prevalence of breast cancer among women, the implementation of a specific protocol of Pilates solo and belly dancing for patients with breast cancer is important, considering the necessity to improve their physical and psychological quality of life. Pilates solo and belly dancing are two types of physical activity that involve mental and physical concentration, music, upper limb movements, femininity, and social involvement. An intervention with these two physical activities could offer options of supportive care to women with breast cancer undergoing treatment, with the aim being to improve physical and psychological quality of life.

**Trial registration:**

ClinicalTrials.gov, NCT03194997. Registration date 12 August 2017. Universal Trial Number (World Health Organization), U1111-1195-1623.

## Background

Cancer is a global public health issue [1, 2]. Among the different types of cancer, breast cancer specifically is the most common among women worldwide [1, 3]. In Brazil, breast cancer is also considered the most common type of cancer among women [4]. Following the many advances in breast cancer treatment, there has been an increase in the 5-year survival rate from 78% to 87% in Brazil [4].

Despite the increase in the survival rate, breast cancer is a significant event in the patient’s life because of the serious side effects of clinical treatment [5], which compromise the patient’s functional capacity [6] and directly affect quality of life [7]. Living with these symptoms can result in emotional and physical exhaustion for these women [8], so a healthy lifestyle that involves good nutrition and regular physical activity is essential to minimize the psychological and physical side effects of treatment [9].

Considering this context, physical activity after the diagnosis of breast cancer, besides being a protective factor, is also auxiliary to the clinical treatment, minimizing the collateral effects and improving patients’ recovery [5, 9]. The American College of Sports Medicine (ACSM) recommends at least 150 min of moderate physical activity or 75 min of vigorous activity per week for patients with cancer [10]. Resistance training twice per week is also recommended to improve general physical health [10, 11]. A meta-analysis of 33 clinical trials regarding the psychological and physical benefits of physical exercise in women after breast cancer recommended physical activity at all treatment stages [12].

Among all types of physical activity that can relate to the healthcare of women with breast cancer, exercise that involves mind and body, such as Pilates and dance, can be beneficial [13–15]. These two types of activities are pleasant activities [16] that can promote emotional connections [17] and can be considered a moderate physical activity according to the ACSM recommendations.

Pilates solo includes resistance and stretching exercises synchronized with breathing, and it respects the principles of control, precision, centering, fluidity of movement, and concentration [18]. It promotes physical benefits for patients regarding functional capacity and muscle strength [19], and most exercises are performed in a position of dorsal decubitus [20] with control of speed, precision, and movement quality promoting the relaxation of the body [21], aspects that are considered consequences of breast cancer treatments, and therefore their recovery becomes essential.

Dance accompanied by music promotes movements with awareness of the body’s rhythms [22]. Belly dance specifically is directed only for women and is considered a form of exercise that associates body and mind through body movements involving especially the upper limbs and performed to the sound of traditional Arabic music [23, 24]. Because it is a dance that involves worship of the earth and the woman’s uterus, as well as feminine sensuality [24, 25], it can act in the rescue of femininity, softness, and beauty, exploring self-confidence and self-esteem of patients [23]. It is a modality of upper limb movement by controlling the arms using veils, tambourines, and vessels, and in this way it can promote physical benefits, considering the consequences of surgery and treatment in these patients [26].

Both the Pilates solo and dance have been the target of studies investigating physical exercise in patients after the diagnosis of breast cancer. Clinical trials that address the Pilates solo method demonstrate its benefits in several aspects, such as improving quality of life, functional capacity, and depressive symptoms [27], as well as benefits for muscle strength, pain, and upper limb functionality, after 8 weeks of treatment [19]. Also, improvements have been noted in external rotation and shoulder abduction in patients subjected to axillary emptying [21] and in shoulder range of motion (ROM), quality of life, body image, and mood after 12 weeks of intervention [14]. None of these studies had published protocols in Pilates solo methods for women with breast cancer.

There are several studies in the literature involving the effects of dance in patients with breast cancer [15, 17, 22, 26, 28–34]. However, published protocols for this population have not been identified; only two of these studies are characterized as randomized controlled trials [22, 33]. The modalities investigated included specific dance therapy methods [15, 17, 28–30, 33], classical ballet and jazz [31], traditional Greek dance associated with muscular strength training of the upper limbs [22], and the practice of circular dance [32] and ballroom dance for couples [33]. Belly dance is also investigated as a pilot study of our research group, identifying benefits in depressive symptoms, fatigue, and quality of life of women with breast cancer while undergoing treatment and after the treatment stage [26].

Thus, it is important to implement a specific protocol of dance and Pilates solo for patients with breast cancer because it has already been positively correlated with the health of women after diagnosis. For this study, belly dance was chosen as the modality of dance included in the protocol, considering the necessity of preserving the femininity of women during the disease [35]. Belly dancing can also address the physical and psychological needs of patients. Furthermore, this type of dance is a form of physical activity that associates the body and mind through movement, particularly involving the upper limbs, to the sound of traditional Arabic music [23–25]. This type of dance can also enhance the emotional aspects of women after the diagnosis of breast cancer because this practice involves expressive movements that facilitate the preservation of femininity, softness, beauty, trust, and security [23]. The Pilates solo was chosen because it favors lymphatic and blood drainage, improves posture, intensifies flexibility, and increases ROM and muscular strength [36]. When breathing exercises are added, the proposed exercises stimulate the thoracic lymphatic system, and thus they can promote a reduction in lymphedema, which improves muscle function and consequently improves quality of life [37].

This study protocol describes a randomized controlled trial of Pilates solo and belly dance (three times per week) for women after the diagnosis of breast cancer and compare its effects with a control group without intervention. The hypothesis is that the Pilates solo and belly dance protocol will promote improvement in primary (quality of life) and secondary (psychological and physical) outcomes in women after the diagnosis of breast cancer, providing a beneficial activity option for women with breast cancer. Our second hypothesis is that Pilates will lead to better improvements in the physical variables and belly dance will improve psychological variables.

## Methods

### Study design

This is a single-center, prospective, three-arm randomized clinical trial designed to assess the effects of Pilates solo and belly dance among women undergoing clinical treatment of breast cancer on the primary outcome of quality of life and secondary outcomes of physical aspects, such as cardiorespiratory fitness, lymphedema, physical activity, disabilities of the arm, ROM, strength, and flexibility, and psychological aspects, such as depressive symptoms, body image, self-esteem, fatigue, pain, sexual function, and sleep quality. Participants will be randomized to either a Pilates solo intervention group, a belly dance intervention group, or the control group. This study is conducted according to the Standard Protocol Items: Recommendations for Interventional Trials (SPIRIT) 2013 checklist: recommended items to address in a clinical trial protocol and related documents (Additional file 1).

### Ethical approval

This study will be conducted in compliance with the Declaration of Helsinki (1975), and it was approved by the Committee of Ethics in Research with Human Beings (CEPSH) of the Santa Catarina State University (UDESC) and the Ethics Committee of the Oncology Research Center (CEPON) under protocol no. 2.073.549 on May 19, 2017. This trial is registered at ClinicalTrials.gov with identifier NCT03194997. Any important protocol deviations or modifications will be communicated to CEPSH and the Clinical Trials website to approval, except when necessary to eliminate apparent immediate hazard(s) to human subjects. Also, the trial participants, trial registries, and the journal to which the protocol is submitted will be informed.

### Participants

The study will be conducted in the city of Florianópolis – State of Santa Catarina, Brazil. The participants will be women diagnosed with breast cancer who will be undergoing treatment in the Oncology Research Center (CEPON) at the time of data collection. The group will receive an explanation of the stages of the study, and after they provide consent to participate, they will sign an informed consent form and then be provided with an initial paper questionnaire for data collection.

### Eligibility criteria

The inclusion criteria are women aged 18 years or older, clinical stage 0 to III breast cancer, receiving adjuvant treatment with hormone therapy in CEPON at any time of the treatment cycle, and receiving the release of the oncologist responsible for the practice of physical activity or the physical therapy sector of CEPON. Exclusion criteria include the diagnosis of some orthopedic or neurological limitation that prevents the practice of physical activity, such as Parkinson’s disease, Alzheimer’s disease, or use of a wheelchair.

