### Randomization and blinding process

The randomization of the sample will be performed by one of the researchers, who should have access to a list of patients with breast cancer (stages 0–III) who were receiving adjuvant treatment with hormone therapy at CEPON in the past 3 years, with the intention to achieve adequate participant enrollment to reach the target sample size. From this list, randomization will be carried out via a website (http://www.randomization.com), which will predict the allocation of patients in the three groups: group A, intervention with belly dance; group B, intervention with Pilates solo; and group C, control group that will be requested to maintain routine activities. The randomization will be stratified by age, dividing the patients between those younger and those older than 60 years of age, considering those older than 60 years of age, according to the Brazilian Statute of the Elderly, established by Law No. 10,741, dated October 1, 2003.

The data from the patients will be maintained only with the principal researcher to protect confidentiality before, during, and after the trial. Because the protocol is difficult to blind for the subjects and the instructors inasmuch as there is no proper way to perform sham physical exercise, all the data analysis will be performed by an external researcher. In this way, at least the data analysis will not be subject to interference.

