### Control group

Women allocated to this group will be asked to continue their routine activities during the 16-week intervention period. They will be contacted every 2 months by telephone. The intervention will be offered to this group in three meetings during the 16 weeks of the intervention. The first meeting will focus on stretching exercise to be performed at home on a regular basis, a second meeting will be about self-esteem, and the last meeting will be about prevention of lymphedema. These meetings will occur with the purpose of promoting an environment where these women can talk and share their experiences with other women with breast cancer and make sure that they also receive health education information, because they will not receive the exercise intervention in the first phase of the study. These meetings were a requirement of the Ethics Committee of CEPON, a hospital that will take part in the study in Brazil, to ensure that the control group also receives possible benefits of the study. Likewise, this strategy can improve the adherence of the control group because they will feel like a group and create social bonds.

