#### Physical activity

The physical activity level will be investigated through the International Physical Activity Questionnaire (IPAQ–short version) [52]. The Brazilian validation and reproducibility were performed by Matsudo et al. [53] and had significant Spearman correlation and high reproducibility (rho = 0.69–0.71; *P* < 0.01) and validity of 0.75 observed compared with the instrument Computer Science & Applications (CSA; ActiGraph, Pensacola, FL, USA). It consists of six items that seek to verify the number of times the subject has practiced at least 10 continuous minutes of walking, moderate and vigorous physical activity, in the last week, in diverse involvements, namely labor, domestic, leisure, recreational, and sports. After completing the questionnaire, the participants can be classified into categories of sedentary, insufficiently active, and very active. The IPAQ also addresses the sitting time of individuals on weekdays and on weekends. There are two specific questions that ask: (1) How much time in total do you spend sitting on a weekday? and (2) How much time in total do you spend seated during on a weekend day? Data are presented in minutes per week.

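### Women who already practise Pilates or belly dance can enter any arm, and baseline activity is neither stratified nor adjusted for, so the contrast may be diluted by an unknown amount and activity may be unbalanced by chance

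*Protocol article*

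**What the plan says.** **Entry.** Eligibility criteria gives the inclusion rules: "The inclusion criteria are women aged 18 years or older, clinical stage 0 to III breast cancer, receiving adjuvant treatment with hormone therapy in CEPON", plus release for physical activity by the oncologist or the physical therapy sector. On the other side, "Exclusion criteria include the diagnosis of some orthopedic or neurological limitation that prevents the practice of physical activity". No criterion there or elsewhere in the article refers to current or recent Pilates, dance or other exercise.

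**Control instruction.** The abstract describes the control condition as a booklet and "maintenance of habitual physical activity routine". Randomization and blinding process has "group C, control group that will be requested to maintain routine activities", and Control group repeats the request for the 16 weeks.

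**Use of baseline activity.** IPAQ (short version) is taken at baseline and at every later visit (Table 3). Women can be "classified into categories of sedentary, insufficiently active, and very active". Stratification is by age only, at 60 years. Statistical analysis names four confounders: type of treatment, type of surgery, age and weight status. Baseline activity is not among them.

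**Planned effect.** Sample size uses 6.15 ± 9.4, the pilot's average before-after difference over the quality-of-life scales, with variance 89.49, and arrives at 19 per group after a 30% margin.

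**The concern.** The trial is meant to show what a Pilates or belly dance programme adds to habitual routine, and the last paragraph of the Background describes the comparator as a group without intervention. As the criteria stand, a woman already attending Pilates or belly dance classes is eligible. If she is allocated to her own modality, she is given something she already has. If she is allocated to control, she is asked to carry on with it. In either case she contributes less to the contrast than the trial assumes.

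Two things are at stake. One is dilution: the observed difference would understate what the programme does for women who do not already practise it. The other is chance imbalance: with small arms and stratification on age alone, the share of already active women can differ between arms, and the analysis as described would not adjust for it.

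**Working it through.** **Step 1: the plan's own figure.** Inputs from Sample size: z-values 1.64 and 0.84, variance 89.49, difference 6.15.

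n = (1.64 + 0.84)² × 89.49 / 6.15² = 6.1504 × 89.49 / 37.8225 = 14.55

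14.55 × 1.3 = 18.9, so 19 per group. The stated figure reproduces, with no reserve for a smaller contrast. (Whether this formula suits the planned comparison is a separate matter. It is used here only on the plan's own terms.)

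**Step 2: where dilution arises.** Assume that a share p of women in every arm already has the benefit at baseline and gains nothing more. The documents do not give p. Let Δ be the effect in the other women.

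- Change from baseline: an active arm gains (1 − p)Δ on average and the control arm gains 0. The difference is (1 − p)Δ. All the loss comes from the active arm.
- Post-intervention level, measured from the level of a woman without the benefit: all women in an active arm have it (Δ), and so does a share p of controls (pΔ). The difference is again (1 − p)Δ.

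The size is the same either way. On the change scale, which is what a group-by-time comparison uses, the already active controls are not its source.

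**Step 3: numbers.** Δ = 6.15 is a before-after change from the pilot, used here as a stand-in for a between-arm effect. The last column is the plan's formula: 14.55 / (1 − p)² × 1.3, rounded up.

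| Assumed p | 6.15 × (1 − p) | n per group |
|---|---|---|
| 0 | 6.15 | 18.9 → 19 |
| 5% | 5.8 | 21.0 → 21 |
| 10% | 5.5 | 23.4 → 24 |
| 20% | 4.9 | 29.6 → 30 |

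If already active women still gain a fraction g of the effect, the difference is 6.15 × [1 − p(1 − g)]. At p = 20% and g = 0.5 this is 6.15 × 0.9 = 5.5 instead of 4.9.

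**Step 4: chance imbalance.** Let each arm hold a Binomial(19, q) number of already active women, where q is an assumed prevalence. A gap of 20 percentage points or more means at least 4 women (0.20 × 19 = 3.8). Exact probabilities:

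| Assumed q | Two given arms | Some pair of the three |
|---|---|---|
| 5% | 1% | 3% |
| 10% | 6% | 13% |
| 20% | 15% | 32% |
| 30% | 21% | 43% |

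These figures would hold for any unstratified characteristic of that prevalence in arms of 19. They follow from the arm size and not from the entry criteria as such.

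**The case against.** A reader might infer that controls who already exercise are what shrinks the contrast. The documents do not support this. The planned analysis is a two-way repeated-measures ANOVA that includes baseline. A control who trains before entry and keeps her routine has that benefit in her baseline score, so her expected change is about zero, like that of any other control. In change, the loss lies with already active women in the Pilates and dance arms.

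A reader might also infer that nothing in the design deals with the matter and that a null result could not be interpreted. That goes too far. Randomisation gives every arm the same expected share of active women, so dilution and chance imbalance are at issue, not systematic bias. The model uses each woman's baseline. IPAQ is recorded in all arms at every visit, so baseline activity and activity in the control arm can be described beside the result.

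Three further objections carry weight. Testing added classes against habitual routine in all medically cleared women is a coherent pragmatic question, and the Discussion stresses generalisation. The IPAQ as described also counts work and domestic activity, so its top category does not show that a woman trains, still less that she does Pilates or dance. And the trial was already enrolling, so a new exclusion would put women entered under two sets of criteria into one small trial.

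What remains is narrower. No criterion addresses current practice of the very modalities under test, and a baseline measure of activity is collected but not named for adjustment. The word "include" in the exclusion sentence may leave the list open, but the article gives no further criterion.

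**Conclusion.** The point holds in a limited form. Women who already practise Pilates or belly dance are eligible for every arm, and neither the stratification nor the named adjustment variables take account of baseline activity. The contrast may therefore be diluted, and baseline activity may be unbalanced by chance.

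The size cannot be derived from the documents, which give no share of such women. The loss of 0.3, 0.6 or 1.2 points from 6.15 at 5%, 10% or 20% assumes the same share in every arm, no further gain in those women, and the pilot's before-after change as the effect. It is smaller if they still gain partly, and negligible if they are rare. The text does not establish that the trial is biased, or that all regular exercisers must be kept out.

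**What to change.** 1. **Statistical analysis.** Add baseline IPAQ activity to the adjustment variables. Use the baseline value only, since later IPAQ values are outcomes. The data are already collected, and the cost is one or two degrees of freedom. This deals with chance imbalance and may help precision. It does not undo dilution, and it is an imperfect marker because IPAQ also counts work and domestic activity.

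2. **Eligibility criteria, for women still to be enrolled.** Add an exclusion for current practice of Pilates or belly dance, screened by one question at recruitment. This is the part that limits dilution. The cost is a slightly smaller recruitment pool and an amendment whose date, with the number of women enrolled before and after it, must be reported.

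Excluding all regular exercisers, or former participants in the belly dance pilot, is optional. The first would narrow the question the trial answers. For the second, the article does not say whether pilot participants could be on the recruitment list.
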